|------------------------------------------------------------------------|----------------------------------------------------------------------------------------------------------------------------------------------------------------------------------------------------------------------------------------------------------------------------------------------------------------------------------------------------------------------------------------------------------------------------------------------------------------------------------------------------------------------------------------------------------------------------------------------------------------------------------------------------------------------------------------------------------------------------------------------------------------------------------|
| Test product:
Dose:
Mode of administration: | ZYH1
4mg once daily (OD)
Oral                                                                                                                                                                                                                                                                                                                                                                                                                                                                                                                                                                                                                                                                                                                                              |
| Reference therapy:                                              | NA                                                                                                                                                                                                                                                                                                                                                                                                                                                                                                                                                                                                                                                                                                                                                                               |
| Duration of treatment :                                         | 12 weeks                                                                                                                                                                                                                                                                                                                                                                                                                                                                                                                                                                                                                                                                                                                                                                         |
| Criteria for efficacy                                           | Primary Efficacy (Time frame 6 and 12 weeks): 
 
• TG
 
 Secondary Efficacy (Time frame 6 and 12 weeks): 
 
• LDL
 
• VLDL
 
• HDL
 
• Total cholesterol
 
• Non HDL Cholesterol (Measured value)
 
• Apo (a)
 
• Apo B
 
• Fasting insulin and C-peptide for HOMA beta & IR
 
                                                                                                                                                                                                                                                                                                                                       |
| Criteria for safety:                                            | 
 
• General and Systemic Clinical Examination: cardiovascular system (CVS), respiratory system (RS), gastrointestinal system (GI), central nervous system (CNS) etc.
 
• Laboratory Investigations: Complete blood count (CBC), aspartate transaminase (AST), alanine transaminase (ALT), alkaline phosphatase (ALP), total bilirubin, γ- glutamyl transpeptidase (GGT), Serum proteins, Blood urea nitrogen (BUN), Serum creatinine and Creatinine phosphokinase (CPK)
 
• Frequency and severity of adverse events (AEs) for all subjects enrolled will be recorded. All AEs, will be classified using 
 
▪ causality
 
▪ severity
 
▪ seriousness
 
 
 
 |

**Statistical methods:**

The SAS® package (SAS® Institute Inc., USA, and Version 9.1.3) will be used for statistical evaluation.

The demographic and baseline characteristics will be summarized. For continuous measurements such as age, the mean, median, standard deviation and range will be tabulated. For categorical measurements such as gender, the frequencies will be computed.

The primary efficacy variable is the Reduction in Triglyceride (TG) at Week 6 and 12 of the treatment period compared with baseline. The change from baseline will be determined as the difference between the means for the treatment period (Week 6 and 12) and the baseline.

For the efficacy endpoints, treatment effect will be evaluated using an analysis of variance (ANOVA) model. Treatment effects will be estimated using the least-square means and 95% confidence intervals (CIs) from the ANOVA model. Statistical significance will be defined as a two-sided p-value <0.05.

|                                                         |                                                  |                                                           |
|---------------------------------------------------------|--------------------------------------------------|-----------------------------------------------------------|
| Prepared by:
[name]
Date: 22.06.2010 | Approved by:
[name]
Date: 22.06.2010 | Protocol No. ZYH1.09.003.01 .PROT
Version No.: 1.0 (R) |
|---------------------------------------------------------|--------------------------------------------------|-----------------------------------------------------------|

|                                                                                   |                                                                                                   |                     |
|-----------------------------------------------------------------------------------|---------------------------------------------------------------------------------------------------|---------------------|
| [figure not shown] | 
Clinical trial Protocol for ZYH1 – Phase II
ZYH1.09.003.01.PROT
 
DCGI Submission
 | 
Confidential
 |
|-----------------------------------------------------------------------------------|---------------------------------------------------------------------------------------------------|---------------------|

All other secondary endpoints would be analysed using appropriate statistical methods.

Intent-to-treat (ITT) and/or Per Protocol (PP) analysis will be carried out for the study trial. The PP analysis will be considered definitive while the ITT analysis will be considered supportive during the trial analysis. All the subjects enrolled in the study will be considered for the safety analysis.

For safety analysis the frequency tabulations of abnormal physical examination and abnormal clinical laboratory findings ( $\geq 5$  UNL) will be presented for each treatment group. Summary statistics for clinical laboratory findings and vital signs will be presented. A list of concomitant medications taken during the study period will be summarised.

All adverse events seen during the study period will be listed.

All statistical analyses will be further described in the Statistical Analysis Plan.

|                                                                  |                                                           |                                                                   |
|------------------------------------------------------------------|-----------------------------------------------------------|-------------------------------------------------------------------|
| 
Prepared by:
[name]
Date: 22.06.2010
 | 
Approved by:
[name]
Date: 22.06.2010
 | 
Protocol No. ZYH1.09.003.01 .PROT
Version No.: 1.0 (R)
 |
|------------------------------------------------------------------|-----------------------------------------------------------|-------------------------------------------------------------------|

|                                                                                   |                                                                                           |              |
|-----------------------------------------------------------------------------------|-------------------------------------------------------------------------------------------|--------------|
| [figure not shown] | Clinical trial Protocol for ZYH1 – Phase II
ZYH1.09.003.01.PROT

DCGI Submission | Confidential |
|-----------------------------------------------------------------------------------|-------------------------------------------------------------------------------------------|--------------|

### ABBREVIATIONS

|         |                                                     |
|---------|-----------------------------------------------------|
| ADA     | American Diabetes Association                       |
| AE      | adverse event                                       |
| ALP     | alkaline phosphatase                                |
| ALT     | alanine aminotransferase                            |
| Apo     | Apoprotein                                          |
| AST     | aspartate aminotransferase                          |
| BMI     | body mass index                                     |
| BP      | Blood pressure                                      |
| BUN     | blood urea nitrogen                                 |
| CD4     | Cluster of Differentiation 4                        |
| CHL     | Cadila healthcare limited                           |
| CNS     | central nervous system                              |
| CPK     | creatinine phosphokinase                            |
| CRF     | case report form                                    |
| CVD     | cardiovascular disease                              |
| CVS     | cardiovascular system                               |
| DM      | diabetes mellitus                                   |
| ECG     | Electrocardiogram                                   |
| EEG     | Electroencephalogram                                |
| FPG     | fasting plasma glucose                              |
| GCP     | Good Clinical Practice                              |
| GFR     | glomerular filtration rate                          |
| GGT     | Gamma glutamyl transpeptidase                       |
| GI      | gastro-intestinal                                   |
| HAART   | highly active antiretroviral therapy                |
| Hb      | Haemoglobin                                         |
| HbA1c   | glycosylated haemoglobin                            |
| HCT     | Hematocrit                                          |
| HDL     | high density lipoprotein                            |
| HIV     | Human immunodeficiency virus                        |
| HOMA    | Homeostasis model assessment                        |
| HOMA IR | Homeostasis model assessment for insulin resistance |
| hs-CRP  | high sensitivity C-reactive protein                 |
| ICU     | Intensive care unit                                 |
| kcal    | Kilocalorie                                         |
| LDL     | low density lipoprotein                             |
| MCH     | mean corpuscular haemoglobin                        |
| MCHC    | mean corpuscular haemoglobin concentration          |

|                                                         |                                                 |                                                           |
|---------------------------------------------------------|-------------------------------------------------|-----------------------------------------------------------|
| Prepared by:
[name]
Date: 22.06.2010 | Approved by:
[name]
Date:22.06.2010 | Protocol No. ZYH1.09.003.01 .PROT
Version No.: 1.0 (R) |
|---------------------------------------------------------|-------------------------------------------------|-----------------------------------------------------------|

|                                                                                   |                                                                                           |              |
|-----------------------------------------------------------------------------------|-------------------------------------------------------------------------------------------|--------------|
| [figure not shown] | Clinical trial Protocol for ZYH1 – Phase II
ZYH1.09.003.01.PROT

DCGI Submission | Confidential |
|-----------------------------------------------------------------------------------|-------------------------------------------------------------------------------------------|--------------|

|      |                                             |
|------|---------------------------------------------|
| MCV  | mean corpuscular volume                     |
| MI   | Myocardial infarction                       |
| OD   | once daily                                  |
| PI   | Protease inhibitor                          |
| PPAR | peroxisome proliferator-activated receptors |
| RBC  | red blood cell                              |
| RS   | respiratory system                          |
| SAE  | serious adverse event                       |
| TC   | total cholesterol                           |
| TG   | Triglyceride                                |
| TZD  | Thiazolinedione                             |
| VLDL | very low density lipoprotein                |
| WBC  | white blood cell                            |
| ZRC  | Zydus Research Centre                       |

|---------------------------------------------------------|-------------------------------------------------|-----------------------------------------------------------|

|                                                                                  |                                                                                           |              |
|----------------------------------------------------------------------------------|-------------------------------------------------------------------------------------------|--------------|
| [figure not shown] | Clinical trial Protocol for ZYH1 – Phase II
ZYH1.09.003.01.PROT

DCGI Submission | Confidential |
|----------------------------------------------------------------------------------|-------------------------------------------------------------------------------------------|--------------|

## 1. INTRODUCTION

### 1.1 MEDICAL BACKGROUND

The prognosis of HIV infection has drastically changed after the introduction of combination antiretroviral therapy often referred to as highly active antiretroviral therapy (HAART). But, lifelong exposure to HAART puts patients at a significant risk for long term metabolic adverse effects including lipodystrophy, insulin resistance, hyperlipidemia and increased cardiovascular morbidity.

HIV lipodystrophy affects up to 50%-80% of patients receiving anti retroviral therapy. Patients with this condition develop a pattern of redistribution in body fat characterised by peripheral fat loss (facial and limb lipoatrophy) and central fat accumulation (buffalo hump, increased breast size and abdominal girth). Although linked to antiretroviral therapy, the exact etiology of HIV lipodystrophy remains unclear. The protease inhibitor (PI) class of anti-retrovirals, used in combination regimens for the treatment of HIV, has been associated with detrimental lipid changes. Recognised metabolic disturbances include abnormalities in both Triglyceride and cholesterol levels in the blood. Resultant cholesterol abnormalities tend to include elevation of LDL and VLDL concentrations.

### 1.2 RATIONALE FOR CONDUCTING THE TRIAL

A variety of drugs have been studied to determine their influence on lipid profiles in patients suffering from HIV associated lipodystrophy due to HAART. Although hypolipidemic diets and physical exercise have also been found to have a role to play in the management of dyslipidemic HIV-infected patients, and are likely to be effective in this group, no randomised studies using these as monotherapy have been performed.

Recent research publications have shown the use of two lipid-lowering class of drugs, statins and fibrates, antiretroviral switching strategies and use of insulin-sensitising drugs. However, no single therapy is able to reach desirable clinical end point for HIV associated lipodystrophy. In order for firm management recommendations to be made in this setting, randomised trials are necessary.

|                                                         |                                                 |                                                           |
|---------------------------------------------------------|-------------------------------------------------|-----------------------------------------------------------|
| Prepared by:
[name]
Date: 22.06.2010 | Approved by:
[name]
Date:22.06.2010 | Protocol No. ZYH1.09.003.01 .PROT
Version No.: 1.0 (R) |
|---------------------------------------------------------|-------------------------------------------------|-----------------------------------------------------------|

|                                                                                  |                                                                                           |              |
|----------------------------------------------------------------------------------|-------------------------------------------------------------------------------------------|--------------|
| [figure not shown] | Clinical trial Protocol for ZYH1 – Phase II
ZYH1.09.003.01.PROT

DCGI Submission | Confidential |
|----------------------------------------------------------------------------------|-------------------------------------------------------------------------------------------|--------------|

ZYH1 is a novel predominately PPAR  $\alpha$  agonist. It is expected to favorably modulate lipid and glucose profile and ameliorate insulin resistance as demonstrated in phase II studies with ZYH1. Thus, based on the above hypotheses and the results of phase II study, we now propose to undertake a prospective, multi-centric, open-label, single arm study to evaluate the safety and efficacy of 4mg of ZYH1 in hypertriglyceridemia in HIV associated lipodystrophy.

### 1.3 DRUG PROFILE

ZYH1, a dual PPAR agonist with predominantly PPAR $\alpha$  and a moderate PPAR  $\gamma$  agonist activity, is (S)- $\alpha$ -Ethoxy-4-{2-[2-methyl-5-(4-methylthio)phenyl]-1H-pyrrol-1-yl]-ethoxy}-benzenepropanoic acid magnesium salt.

For this study, safety and efficacy of 4mg of ZYH1 developed by Cadila Healthcare Ltd will be evaluated in hypertriglyceridemia in HIV associated lipodystrophy.

|                                                         |                                                 |                                                           |
|---------------------------------------------------------|-------------------------------------------------|-----------------------------------------------------------|
| Prepared by:
[name]
Date: 22.06.2010 | Approved by:
[name]
Date:22.06.2010 | Protocol No. ZYH1.09.003.01 .PROT
Version No.: 1.0 (R) |
|---------------------------------------------------------|-------------------------------------------------|-----------------------------------------------------------|

|                                                                                  |                                                                                           |              |
|----------------------------------------------------------------------------------|-------------------------------------------------------------------------------------------|--------------|
| [figure not shown] | Clinical trial Protocol for ZYH1 – Phase II
ZYH1.09.003.01.PROT

DCGI Submission | Confidential |
|----------------------------------------------------------------------------------|-------------------------------------------------------------------------------------------|--------------|

## 2. STUDY OBJECTIVES

### 2.1 GENERAL AIM / PRIMARY OBJECTIVE

To evaluate the safety and efficacy of 4mg of ZYH1 in hypertriglyceridemia in HIV associated lipodystrophy

### 2.2 PRIMARY ENDPOINT(S)

Percent change in TG levels from baseline to Week 6 and Week12.

### 2.3 SECONDARY ENDPOINT(S)

Percent change in the following parameters from baseline to Week 6 and Week 12.

- LDL
- VLDL
- HDL
- Total cholesterol
- Non HDL Cholesterol (Measured value)
- Apo (a)
- Apo B
- Fasting insulin and C-peptide for HOMA beta & IR

|                                                         |                                                 |                                                           |
|---------------------------------------------------------|-------------------------------------------------|-----------------------------------------------------------|
| Prepared by:
[name]
Date: 22.06.2010 | Approved by:
[name]
Date:22.06.2010 | Protocol No. ZYH1.09.003.01 .PROT
Version No.: 1.0 (R) |
|---------------------------------------------------------|-------------------------------------------------|-----------------------------------------------------------|

|                                                                                  |                                                                                           |              |
|----------------------------------------------------------------------------------|-------------------------------------------------------------------------------------------|--------------|
| [figure not shown] | Clinical trial Protocol for ZYH1 – Phase II
ZYH1.09.003.01.PROT

DCGI Submission | Confidential |
|----------------------------------------------------------------------------------|-------------------------------------------------------------------------------------------|--------------|

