### 5.2 SAFETY

Following parameters will be assessed

- General and Systemic Clinical Examination: cardiovascular system (CVS), respiratory system (RS), gastrointestinal system (GI), central nervous system (CNS) etc.
- Laboratory Investigations: Complete blood count (CBC), aspartate transaminase (AST), alanine transaminase (ALT), alkaline phosphatase (ALP), total bilirubin, γ- glutamyl transpeptidase (GGT), Serum proteins, Blood urea nitrogen (BUN), Serum creatinine and Creatinine phosphokinase (CPK)
- Frequency and severity of adverse events (AEs) for all subjects enrolled will be recorded.

|                                                         |                                                 |                                                           |
|---------------------------------------------------------|-------------------------------------------------|-----------------------------------------------------------|
| Prepared by:
[name]
Date: 22.06.2010 | Approved by:
[name]
Date:22.06.2010 | Protocol No. ZYH1.09.003.01 .PROT
Version No.: 1.0 (R) |
|---------------------------------------------------------|-------------------------------------------------|-----------------------------------------------------------|

|                                                                                  |                                                                                           |              |
|----------------------------------------------------------------------------------|-------------------------------------------------------------------------------------------|--------------|
| [figure not shown] | Clinical trial Protocol for ZYH1 – Phase II
ZYH1.09.003.01.PROT

DCGI Submission | Confidential |
|----------------------------------------------------------------------------------|-------------------------------------------------------------------------------------------|--------------|

- All AEs, will be classified using
  - causality
  - severity
  - seriousness

|                                                         |                                                 |                                                           |
|---------------------------------------------------------|-------------------------------------------------|-----------------------------------------------------------|

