| Efficacy studies:
Laboratory:
1. Triglyceride
2. LDL
3. VLDL
4. HDL
5. Total cholesterol
6. Non HDL Cholesterol
7. Apo(a)
8. Apo B
9. Fasting insulin and C-peptide for HOMA beta & IR | ✓                                                    |                     | ✓                   | ✓                    |
| Laboratory studies(safety)
1. CBC
2. LFT
3. RFT
4. CPK                                                                                                                                                   | ✓                                                    | ✓                   | ✓                   | ✓                    |
| ECG                                                                                                                                                                                                                  | ✓                                                    |                     |                     | ✓                    |
| Pregnancy test for female subjects (advise for contraception)                                                                                                                                                        | ✓                                                    |                     |                     |                      |
| Dispensing of Study Medication                                                                                                                                                                                       | ✓                                                    | ✓                   | ✓                   |                      |
| Study Medication Tablet Count                                                                                                                                                                                        |                                                      | ✓                   | ✓                   | ✓                    |
| Recording of Adverse Events                                                                                                                                                                                          |                                                      | ✓                   | ✓                   | ✓                    |

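### HOMA-beta and HOMA-IR are planned secondary measures, but no visit measures the fasting glucose they need

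*Protocol*

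**What the plan says.** Section 2.3 defines the secondary endpoints as "Percent change in the following parameters from baseline to Week 6 and Week 12", and the last item in the list is "Fasting insulin and C-peptide for HOMA beta & IR". Section 5.1.2 repeats the item, and so do both secondary efficacy lists in the synopsis.

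Table 1 (in the synopsis and in Section 6.3) schedules the efficacy laboratory tests at Visit 1, Week 6 and Week 12. It numbers nine items. Eight are lipids and apolipoproteins, and the ninth is "9. Fasting insulin and C-peptide for HOMA beta & IR". The safety laboratory row, at all four visits, reads "1. CBC 2. LFT 3. RFT 4. CPK". Section 5.2 spells that panel out as blood count, liver enzymes and bilirubin, proteins, urea nitrogen, creatinine and CPK.

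The term "fasting plasma glucose" occurs only in the abbreviation list. The one reference to glucose in the body text is in Section 1.2, which says of the drug: "It is expected to favorably modulate lipid and glucose profile and ameliorate insulin resistance".

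**The concern.** HOMA indices are computed from fasting glucose paired with fasting insulin or C-peptide. The protocol states that the two hormones are collected for HOMA, yet it schedules only the hormone half of the calculation. A site that follows Table 1 exactly would complete the trial without the data for either index.

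The insulin-resistance part of the drug's rationale would then go untested on the measure the protocol chose for it, and the trial would hold no scheduled glucose values for a drug expected to alter glucose. This is a gap in data collection. The samples belong to fixed visits on treatment and cannot be retaken afterwards, so it has to be closed before enrolment.

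**Working it through.** The protocol states no figure to reproduce here. The check is an inventory of scheduled tests against the inputs HOMA needs, followed by an illustration of why glucose cannot be assumed.

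**Inputs needed.** The protocol gives no HOMA formula. The standard ones, with insulin in uU/mL and glucose in mg/dL, are:

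- HOMA-IR = insulin x glucose / 405
- HOMA-beta = 360 x insulin / (glucose - 63)

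The computer-model version also needs fasting glucose, paired with insulin or C-peptide, so C-peptide does not replace it. Percent change to Weeks 6 and 12 requires glucose at three times: baseline, Week 6 and Week 12.

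**Inputs scheduled.**

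| Place in protocol | Laboratory tests | Glucose? |
|---|---|---|
| Table 1, efficacy row (both copies) | TG, LDL, VLDL, HDL, total cholesterol, non-HDL, Apo(a), Apo B, insulin and C-peptide | No |
| Table 1, safety row (both copies) | CBC, LFT, RFT, CPK | No |
| Section 5.2 and the two synopsis safety lists | CBC, AST, ALT, ALP, bilirubin, GGT, proteins, BUN, creatinine, CPK | No |
| Section 6.2, pre-enrolment tests | Unspecified tests to rule out other disease | None named; could not supply Week 6 or Week 12 |

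Scheduled glucose measurements: 0 of 3.

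**Could a typical glucose value be substituted?** The values below are assumed for illustration and do not come from the protocol. With insulin fixed at 15 uU/mL:

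| Glucose (mg/dL) | HOMA-IR | HOMA-beta |
|---|---|---|
| 80 | 15 x 80 / 405 = 2.96 | 5400 / 17 = 317.6 |
| 100 | 15 x 100 / 405 = 3.70 | 5400 / 37 = 145.9 |
| 125 | 15 x 125 / 405 = 4.63 | 5400 / 62 = 87.1 |

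The endpoint is a within-subject percent change, so the more relevant case is a change between visits. Take insulin falling from 15 to 12 (-20%) from a baseline glucose of 100, where HOMA-IR is 3.70 and HOMA-beta is 145.9:

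| Glucose at follow-up | HOMA-IR change | HOMA-beta change |
|---|---|---|
| 90 (-10%) | (12 x 90) / (15 x 100) - 1 = -28% | (4320 / 27) / (5400 / 37) - 1 = +9.6% |
| 100 (0%) | (12 x 100) / (15 x 100) - 1 = -20% | (4320 / 37) / (5400 / 37) - 1 = -20% |
| 110 (+10%) | (12 x 110) / (15 x 100) - 1 = -12% | (4320 / 47) / (5400 / 37) - 1 = -37.0% |

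The same insulin change is compatible with a HOMA-IR fall of 12% to 28%, and with HOMA-beta moving in either direction.

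The protocol gives no reason to treat glucose as fixed. Section 3.2 excludes subjects on insulin or glitazone/glitazar therapy, but it neither excludes diabetes as such nor sets a glucose limit. Section 1.2 expects the drug itself to act on glucose.

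**The case against.** The strongest reply is that the loss is narrow. The listed item is fasting insulin and C-peptide, with HOMA as its stated use. Both hormones are scheduled at all three efficacy visits and their percent changes can be reported. The other seven of the eight secondary items do not depend on glucose. Triglyceride, the primary endpoint, is untouched, as are the sample size and the analysis populations. All of this stands: what is lost is the derived indices, not the whole item.

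A second reply is that sites might run glucose anyway, because naming HOMA in the Table 1 row implies it, and the case report forms are not at hand. That is possible, but Table 1 numbers its tests one by one and the safety panel is itemised analyte by analyte. An endpoint should not depend on a laboratory adding an unlisted test.

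The abbreviation list is weak evidence either way. It also holds terms such as HbA1c and hs-CRP that are scheduled nowhere, which suggests carry-over from a template.

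Deferring to a statistical analysis plan does not help, since such a plan can choose a HOMA formula but cannot supply a measurement that was never made. Nor is the gap a product of how the document was read, because the lists appear in both synopsis and body and agree.

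**Conclusion.** The concern holds. Under the schedule as written, HOMA-IR and HOMA-beta cannot be derived for any of the 50 planned subjects at baseline, Week 6 or Week 12. This rests on two things: that sites perform the listed tests and no others, and that HOMA takes fasting glucose as an input, which is true of both the simple formulas and the computer model. The numerical examples use assumed insulin and glucose values. They show only that glucose cannot be filled in by assumption, and the conclusion does not depend on them.

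The affected measures are secondary, but their loss is complete, cannot be repaired later and is cheap to prevent. The correction should be made before enrolment.

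**What to change.** Add fasting plasma glucose to the efficacy laboratory row of Table 1, in both the synopsis and Section 6.3, at Visits 1, 3 and 4, taken from the same fasting sample as insulin and C-peptide. In Sections 2.3 and 5.1.2 and both synopsis endpoint lists, name glucose as an input to HOMA so that all copies agree. State which HOMA formula or model will be used. Overnight fasting is stated explicitly only under Visit 1, so state it for Visits 3 and 4 in the same edit.

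Summarising glucose itself with the safety laboratory data would be useful given the rationale, but it is optional and not needed to restore the endpoint.

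If the sponsor does not want to measure glucose, the consistent alternative is to delete the HOMA wording throughout and keep insulin and C-peptide as endpoints in their own right.

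The cost is about 50 x 3 = 150 routine assays at visits where blood is already drawn, with no extra visit or procedure, plus a short amendment.
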